## SECONDARY OBJECTIVES

To gain preliminary evidence for the effects of task-specific locomotor practice incorporating visual cues compared to interventions not including visual cues on the ability to trigger gait recovery and adaptability following stroke.

# TRIAL / STUDY DESIGN

## TRIAL / STUDY CONFIGURATION

This is a 3-arm parallel group, multi-centre, pilot, randomised control trial. The experimental group will receive visual cue gait training while the control group will receive conventional over-ground gait training.

### Primary endpoint

To achieve the stated aims, we will: a) Determine the numbers of patients willing to be recruited into both control and VCT groups; b) Determine the willingness of physiotherapists at each collaborating site to enrol patients to both control and VCT groups; c) Determine the numbers of patients who do not complete the allocated treatment, thus dropping out of the study; d) determine the reasons for dropping out; e) Measure completeness of outcome data, i.e. percentage of patients with no missing values in outcome assessments. In order to measure completeness of outcome data, the primary and secondary outcome measures that we proposed to use in the future definitive trial will be carried out as follows :

Primary outcome measures for walking and adaptability of walking respectively:

1. *Proportion of participants achieiving a gait speed of 0.4 m/s and 0.8 m/s*. Gait speed will be measured during a 10 metre walk. Participants will be given a 3 meter warm-up distance and 3 metres to walk beyond the 10 metres, and will walk at their usual pace. The time taken to walk the 10 metres will be recorded. Perry et al ([1995](#_ENREF_35))have shown that these gait speed classifications correspond to walking abilities in the community, with a gait speed of < 0.4 m/s for household walkers, of 0.4 – 0.8 m/s for limited community walkers, and >0.8 m/s for community walkers. It has been demonstrated that progressing from one of these classifications to the next correlates with improvement in physical functioning and quality of life([Schmid, Duncan et al. 2007](#_ENREF_40)) and these categories also correspond with changes in the Functional Ambulation Category, a categorical scale, rating level of skill in functional ambulation([Holden, Gill et al. 1986](#_ENREF_21)).

2.*Measures of adaptability of gait*: Time and number of steps to complete a 90 degree turn & the number of failures to hit targets presented unpredictably in timing and location.

Both turning and walking ability will be assessed using the GaitRite system. Patients will walk or turn on top of the GaitRite instrumented walkway which will measure the number of steps taken to turn and time taken to turn in addition to step widths and lengths during turning (to quantify if stepping strategies used during turning are comparable to what healthy adults are known to employ ([Hollands, Sorensen et al. 2001](#_ENREF_22))). Longer time to turn and increased number of steps to turn have all been identified as performance measures which may be indicative of difficulty turning and increased falls risk([Thigpen, Light et al. 2000](#_ENREF_46), [Dite and Temple 2002](#_ENREF_12)). The number of times participants fail to hit stepping targets when these are presented unpredictably in timing and location will be used to indicate the ability to adapt the straight gait pattern according to environmental demands.

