## PRIMARY OBJECTIVE

Determine the numbers of patients willing to be recruited into both control and VCT groups

Determine the willingness of physiotherapists at each collaborating site to enrol patients to both control and VCT groups

Determine the numbers of patients who do not complete the allocated treatment, thus dropping out of the study, and determine the reasons for dropping out.

Use knowledge gathered about recruitment, outcomes and drop-out rates to determine sample size for a subsequent definitive trial.

Measure completeness of outcome data, i.e. percentage of patients with no missing values in outcome assessments.

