### Expected duration of participant participation

During the active treatment period, participants will attend the outpatient rehabilitation setting for 1hr., two times weekly for 8 weeks. Participants will then be assessed at follow up 3 months after baseline.

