### Removal of participants from therapy or assessments

Participants may permanently discontinue treatment if safety is considered to be at risk e.g. development of comorbidities preventing ability to participate in the treatment, the participant fails to comply with treatment or they withdraw consent. In all of these situations outcome data will continue to be sought at the usual planned time points when the participant and safety permits. Measures will be taken within 5 days following consent and treatment or they will not be included in the dataset at that time point. Given the aims of the study are to determine the numbers of patients who do not complete the allocated treatment, thus dropping out of the study, and determine the reasons for dropping out, withdrawn participants will not be replaced.

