### Participant removal from the study due to adverse events

Participants will be removed from the study following an AE if treating medical team indicate that the participant is no longer able to tolerate walking practice.

#

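### The drop-out endpoint treats stopping treatment as leaving the study, although treatment stoppers are still followed for outcomes, so it is not the attrition figure that sizing the definitive trial needs

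*Protocol*

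**What the plan says.** The primary objective lists, among its aims, "Determine the numbers of patients who do not complete the allocated treatment, thus dropping out of the study, and determine the reasons for dropping out". Item (c) under Primary endpoint repeats the definition: "Determine the numbers of patients who do not complete the allocated treatment, thus dropping out of the study". The same clause stands in the Synopsis objectives and in Removal of participants from therapy or assessments. The next aim under Primary objective is "Use knowledge gathered about recruitment, outcomes and drop-out rates to determine sample size for a subsequent definitive trial".

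Removal of participants from therapy or assessments covers permanent discontinuation of treatment for safety (with new comorbidities as the example), for non-compliance or for withdrawal of consent. It then says: "In all of these situations outcome data will continue to be sought at the usual planned time points when the participant and safety permits". Under Definition of population analysed, the full analysis set turns on having had some treatment and having a post-baseline assessment of the primary endpoint. It does not turn on finishing treatment.

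Participant removal from the study due to adverse events says: "Participants will be removed from the study following an AE", where the treating medical team judges that walking practice can no longer be tolerated. It says nothing about later outcome assessments.

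Two other provisions bear on outcome loss. Item (e) under Primary endpoint is "Measure completeness of outcome data, i.e. percentage of patients with no missing values in outcome assessments"; the Synopsis adds 95% confidence limits. Procedures for missing, unused and spurious data rules out imputation and plans a tabulation of missing data with reasons.

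**The concern.** A pilot of this kind should yield two separate figures. The proportion who do not finish the allocated training is a result about acceptability. The proportion without the primary outcome is the attrition figure by which a later sample size is inflated. The protocol gives the first quantity the name of the second and then names drop-out rates as a sizing input.

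The error can run either way. Someone who stops training part-way but attends both later assessments counts as a drop-out, yet costs the analysis nothing. Someone who attends every session and misses the 3-month visit is not a drop-out, yet has no gait speed at that visit. That second case is possible because the last assessment falls after the 8-week treatment period: "Participants will then be assessed at follow up 3 months after baseline".

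The adverse-event section raises a related problem. A site that reads removal from the study literally could stop collecting outcomes from people whom the other section would still assess. Outcomes not collected cannot be recovered later.

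**Working it through.** **What each endpoint counts.** Four kinds of participant, set against items (c) and (e) and the quantity that sizing needs:

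| Participant | Drop-out under (c) | Complete under (e) | Lacks gait speed |
| --- | --- | --- | --- |
| Stops treatment, fully assessed at both later visits | Yes | Yes | No |
| Stops treatment, not assessed again | Yes | No | Yes |
| Finishes treatment, misses the 3-month visit | No | No | Yes, at 3 months |
| Finishes treatment, one SF-12 item missing | No | No | No |

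Neither (c) nor (e) matches the last column. Item (c) is wrong in rows 1 and 3, and (e) is wrong in row 4.

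**Reproducing a protocol figure.** There is none to reproduce. Sample size and justification gives no formal calculation and no expected drop-out rate. What follows is illustration only.

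**Formulas.** Let *t* be the proportion not completing treatment, *f* the share of those still assessed, and *c* the share of treatment completers with no outcome.

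- Outcome loss: L = t(1 − f) + (1 − t)c
- Inflated size for evaluable number n: N = n/(1 − d), with d the attrition rate used
- Size obtained using t, relative to size needed using L: (1 − L)/(1 − t)

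The two rates agree only when t·f = (1 − t)c.

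**Two cases in 60 participants.** The number 60 is from Randomization and blinding; all other counts are assumed.

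- Case A: 12 stop treatment, 8 of them are still assessed, and 3 completers are lost. Then t = 12/60 = 20% and L = (4 + 3)/60 = 7/60 = 11.7%. The factors are 1/0.80 = 1.25 and 60/53 = 1.132. The ratio 1.25/1.132 = 1.104, so the definitive trial is about 10% too large.
- Case B: 3 stop treatment and are lost, and 9 of the 57 completers are lost. Then t = 3/60 = 5% and L = 12/60 = 20%. The factors are 1/0.95 = 1.053 and 1/0.80 = 1.25. The ratio 1.053/1.25 = 0.842, so the definitive trial is about 16% too small.

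**Range.** Assume n = 200 evaluable and no loss among completers (c = 0):

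| t | N using t | N using L, f = 0 | f = 50% | f = 100% |
| --- | --- | --- | --- | --- |
| 10% | 223 | 223 | 211 | 200 |
| 20% | 250 | 250 | 223 | 200 |
| 30% | 286 | 286 | 236 | 200 |

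In the other direction, t = 20%, f = 0 and c = 10% give L = 0.20 + 0.80 × 0.10 = 28%. Then N = 200/0.72 = 278 is needed, against 250 using t.

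**The two removal passages.** One keeps seeking outcomes after permanent discontinuation, and among its reasons it names comorbidities that prevent taking part in the treatment. The other takes a participant who cannot tolerate walking practice after an adverse event out of the study. The same participant can fall under both, and the protocol does not say which governs outcome collection.

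**The case against.** The strongest reply is that outcome loss is already a primary endpoint. Item (e) stands in the same sentence as item (c), and the missing-data section adds a tabulation with reasons. A completer who misses the 3-month visit is therefore recorded. This largely stands: the pilot will hold the data from which the right rate can be computed. What remains is that (e) is all-or-nothing across every measure, so one missing questionnaire item counts the same as complete loss to follow-up. The tabulation is not tied to gait speed, to time point or to sizing.

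Second, sizing is to draw on recruitment, outcomes and drop-out rates together, and no inflation formula is given. Non-completion is also a legitimate planning input, because under intention to treat it can dilute the effect. Both points stand. A reader might infer that the definitive trial will be wrongly sized; the protocol does not support that. It supports only that the quantity called drop-out is not the one an inflation for attrition needs.

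Third, a reader might infer that the adverse-event rule takes out the participants doing worst and so makes the gait-speed proportions look better than they are. The protocol does not show this. Its wording may be loose, with outcome collection meant to continue, and nothing states how those removed would have walked.

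Finally, detailed tabulation can be left to the analysis plan, which the Statistics section announces as a separate document. That is fair for layout. It does not cover a definition fixed in the primary objective and endpoint, or instructions to sites that determine which outcomes are collected.

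**Conclusion.** The inconsistency is real and is in the current text. Non-completion of treatment is equated with leaving the study, while the protocol's own follow-up rule and analysis set treat them as separate. Item (e) and the missing-data tabulation reduce the consequence but do not supply the proportion lacking gait speed at each time point. The adverse-event passage conflicts with the follow-up rule, and a site following it could stop collecting outcomes; the direction and size of any resulting bias cannot be established.

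The figures of about 10% too large and about 16% too small rest wholly on assumed counts. They also assume that treatment non-completion alone would be used to inflate the sample size, which the protocol does not say. This is a correction worth making, below the level of a fault that undermines the pilot. The endpoint half can be repaired at analysis from records already kept. Outcomes that a site never collected cannot.

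**What to change.** 1. In the Synopsis objectives, Primary objective, Primary endpoint item (c) and Removal of participants from therapy or assessments, delete the clause that turns not completing treatment into leaving the study.
2. Report two quantities, each by arm: treatment non-completion with reasons, presented as an acceptability result; and missing gait speed at post-intervention and, separately, at 3 months. Keep item (e) as it is.
3. Under the sample-size aim, state that the missing-gait-speed rate, at the time point the definitive trial adopts, is the attrition figure used for inflation. Non-completion may still inform the assumed effect.
4. Reconcile Participant removal from the study due to adverse events with Removal of participants from therapy or assessments, so that sites have one instruction on whether outcome collection continues after training stops.

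The cost is amended wording and one or two table rows. The data are already planned: attendance and minutes come from the treatment logs described under Compliance, and gait speed is scheduled at all three assessments in Table 1. There is no material downside.

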### Secondary endpoint

Secondary outcome measures: We hypothesise that VCT training will also have a positive effect on independence of functional walking in the community in terms of adaptability of gait during everyday functional mobility manouvers (e.g. turning, obstacle avoidance), motor impairment walking endurance, balance and falls efficacy. Therefore the following secondary outcome measures are included:

3.Timed up and Go (TUG) test. The TUG is a test of everyday functional mobility requiring participants to stand up from a chair, walk 3m, turn around (180-degrees) walk back to the chair and sit-down. The time taken to complete the test has been shown to have good test-retest reliability in a number of populations including stroke patients ([Ng and Hui-Chan 2005](#_ENREF_31)).

4.Fugl-Meyer Assessment will be used to assess changes in motor and sensory impairment. The assessment includes items for upper and lower limbs, speed, coordination, light touch and proprioception. Items are rated on a three point scale (0= cannot perform, 1 = performs partially, 2 = performs fully) and standardised protocols for administration will be followed ([Gladstone 2002](#_ENREF_17)). Excellent interrater and intrarater reliability and construct validity have been demonstrated for this scale, and preliminary results indicates that it is responsive to change([Gladstone 2002](#_ENREF_17)).

5.Berg Balance Scale This scale has good intra-rater reliability (ICC=.97, ([Berg 1989](#_ENREF_6))) for patients with stroke.

6.A scale to assess mobility of people living in the community after stroke ([Stanko 2001](#_ENREF_43)) in different settings: (i) inside the home (ii) outside the home: access to and from property, outside buildings, clothesline, garden and letterbox (iii) in the community: access to health and shopping facilities, leisure sites and public transport.

8. Falls efficacy scale([Yardley 2005](#_ENREF_48)). This will assess changes in confidence to walk without falling which may be expected as a result of practice of adaptabile walking.

9. Pedometer will be used to record the number of steps taken during treatment sessions to contrast intensity of VCT treatment to usual care.

8.SF-12 . This is a short-form health survey with only 12 questions. It yields an 8-scale profile of functional health and well-being scores, including physical functioning, and social, emotional, mental and general health and has been included to measure effects on broader quality of life([Brazier 1992](#_ENREF_8)).

All outcome measures will be gathered within 5 days following consent and completion of treatment.

### Baseline Data

Baseline assessments will be conducted **PRIOR** to randomisation as recommended in guidelines for good practice in RCTS (MRC), therefore reducing possible recruitment bias.

Prior to randomisation, patients and the clinician will fill out a series of questionnaires (see Table 1) including:

Primary care staff recorded patient demographics (Appendix 1):

1. Known stroke or TIA. Date of stroke, side of stroke, type of stroke – if recorded on the Demographic Front Sheet

3. Known medical history: premorbid conditions such as a concurrent progressive neurologic disorder, acute coronary syndrome, severe heart failure, confirmed or suspected lower-limb fracture preventing mobilization, and those requiring palliative care will be excluded.

Baseline assessor completed:

Baseline assessment of the primary and secondary measures (described above) *and additionally include*

1. An assessment of receptive/expressive aphasia the Sheffield Screening Test for Acquired Language Disorders ([Syder 1993](#_ENREF_44)) **(**Appendix 2**)**
2. The Mini Mental State Examination ([Folstein, Folstein et al. 1975](#_ENREF_14)) to assess cognitive function. **(**Appendix 3**).**
3. Star Cancellation test (Appendix 4)
4. Modified Rankin Scale (Appendix 5)

Table 1: Assessment Schedule. *All measures are completed by blinded assessor except the self report log, which participants complete weekly, themselves.

| Outcome measure | Baseline | Post Intervention (8 weeks post-randomisation) | Follow Up (3 months post-randomisation) |
| --- | --- | --- | --- |
| Gait speed | X | X | X |
| Time & number of steps to turn 90° | X | X | X |
| Timed up and Go | X | X | X |
| Fugl-Meyer | X | X | X |
| Berg Balance Scale | X | X | X |
| Functional ambulation classification | X | X | X |
|  |  |  |  |
| SF 12 | X | X | X |
| Self report log* | X | X | X |
| Falls Efficacy Scale | X | X | X |
| Pedometer |  | During treatment |  |
| Sheffield Screening Test | X |  |  |
| MMSE | X |  |  |
| mRS | X |  |  |
| Star Cancellation test | X |  |  |
| Patient demographics | X |  |  |

**Health economic analysis**

As this is a pilot study, a cost--consequence analysis will be undertaken to present all relevant costs and outcomes associated with VCT and usual care. Cost data collection will be undertaken on all patients within the trial and a simple cost analysis undertaken to compare the cost of a VCT programme with walking training provided in the context of usual care. This will be from a health and social services perspective. The cost of training therapists to deliver both VCT and usual care and the cost of development and production of the treatment manuals will be determined. Details of all equipment and software used for patient therapy will be recorded and costs established. In terms of the delivery of a VCT programme and conventional treatment, therapist time spent with the patient and location of therapy will be recorded in order to calculate the cost of an individual session. Finally, any additional stroke rehabilitation-specific primary and secondary care and social services resource use information will be collected from each patient. Following identification of all the relevant costs, methods for collecting cost data will be piloted (data collection forms, questionnaires), which will provide cost information and enable effective resource use and cost data collection systems to be determined for use in a larger trial. The generic quality of life measure, SF-12, will be administered to patients as part of the trial. This will facilitate the use of the SF-6D, which is a measurement of outcome appropriate for an economic analysis as it allows the calculation of quality-adjusted life years (QALYs). The pilot work will provide preliminary data on the suitability and responsiveness of SF-6D as a measure of outcome for an economic evaluation in a full trial. Within the economic evaluation alongside a larger trial, a cost-effectiveness analysis and cost-utility analysis are proposed to determine the (a) cost per unit reduction in impairment, and (b) cost per quality-adjusted life year gained respectively.

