1. We have carried out a risk / benefit analysis of the all aspects for the study and found that overall the study is a low risk study. The only aspects of the study that raised a medium level of risk were:
   1. An increased risk of falling outside the house. We will specifically record this adverse event in the group who receive both the experimental and control interventions. The level of falls can be easily assessed by the TSC and a decision made regarding participant ethical and safety concerns.
   2. Implementation of the treatment - obtaining agreement from the PCTs to fund the treatment could be difficult, participants may not then receive the experimental intervention as planned
   3. Maintaining blinding (The research assistant will be blind to treatment allocation. However, as they are required to visit participants to complete the assessments, the participant may discuss what has been happening and therefore un-blind the research assistant). We will monitor this effect
   4. Collection of identifiable data for the Medical Research Information Services. We will be using this system to check if a participant is alive before we send any questionnaires. We will follow Research Governance procedures when collecting this information.
   5. Incomplete data, especially from questionnaires. We are using a Clinical trial Unit to collect and store data and to check weekly for incomplete data. We have a policy for increasing the rate of completion that will be followed
2. The pace of recruitment is anticipated to be very swift. If this is the case then the timescale to analyse the data and adjudicate as to proven effectiveness or otherwise of the intervention would mean that most, if not all, participants would already have been recruited by the time such a decision was reached.

[name] (University of Salford) has agreed to be the independent chair of the TSC & DMEC. We have also enrolled [name] (for independent scientific expertise on visual cueing and locomotor control) [name] as a patient representative and [name] (Senior Statistician, University of Glasgow as independent statistician), along with [name] (PI).

Schedule of meetings:

During the first work package fortnightly project meetings involving the grant holders will take place to manage the development phase. Three meetings will be scheduled to form the treatment manuals.

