# ADVERSE EVENTS

There may be a very small increased risk of falling as a result of walking practice and this small risk is stated clearly in the patient information sheet. Every effort will be made to minimise the risk of falls through training the patient and having therapists next to patients at all times. We do not expect any other risks of taking part in the study. Therefore, it is reasonable to collect only targeted treatment-related adverse events and serious adverse events such as ‘falls leading to injury requiring a hospital or GP visit’. Should such an event occur, an adverse event form (Appendix 11) will then be completed by the relevant therapist (forms can also be downloaded from the trial website). Participant fatigue which requires only momentary rest and following which the training session resumes will not be classed as an adverse event and will not require reporting but will be documented through any resulting reduction in treatment time.

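### Read as written, the piloted cost collection leaves out hospital, emergency and GP care for injurious falls, the harm the protocol itself targets

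*Protocol*

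**What the plan says.** The Health economic analysis section of the protocol states its aim and its viewpoint together: "a cost--consequence analysis will be undertaken to present all relevant costs and outcomes associated with VCT and usual care", and "This will be from a health and social services perspective". It then lists what will be costed: training of therapists, the treatment manuals, equipment and software, therapist time and place of treatment. For everything else a participant uses, it gives a single sentence: "any additional stroke rehabilitation-specific primary and secondary care and social services resource use information will be collected from each patient". The forms and questionnaires are to be piloted so that a collection system can be settled for a larger trial, in which cost-effectiveness and cost-utility analyses are proposed.

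On harm, the Adverse Events section says: "There may be a very small increased risk of falling as a result of walking practice". It expects no other risks and gives as its example of a reportable event "falls leading to injury requiring a hospital or GP visit". The Trial Management section calls the study low risk overall but lists "An increased risk of falling outside the house" among the aspects of medium risk, and says these falls will be specifically recorded in the experimental and control groups. The Safety endpoints section gives falls as its example of a spontaneously reported event.

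**The concern.** A cost-consequence analysis is only as complete as the resource-use form behind it. The protocol defines its target adverse event by the need for a hospital or GP visit, and that kind of contact lies outside a form restricted to stroke rehabilitation. An emergency attendance, a fracture admission or a GP consultation after a fall is a health-service cost, but it is not rehabilitation.

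The background section says that a large share of falls after stroke happen during walking and turning, which are the tasks being trained. Fall-related care could therefore differ between arms in either direction. If it does and is not collected, the cost comparison favours whichever arm has more injurious falls. The SF-12, from which SF-6D values are to be derived, could register the health loss from such a fall while the cost side omits its treatment.

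The costing tool is one of the things this pilot sets out to test, so a gap in its scope matters even with no formal testing. Contacts that are not asked about are hard to recover later.

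**Working it through.** The protocol gives no cost figure or event rate to reproduce, so the check is a comparison of text, followed by a note on scale.

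1. **Aim against scope (Health economic analysis).** The aim is all relevant costs; the perspective is health and social services. The wider service use named is primary care, secondary care and social services, each under the stroke rehabilitation qualifier. Care for a fall injury meets the sector description but not the qualifier, so a form built to that sentence would not ask for it.

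2. **Is that care relevant on the protocol's own terms?** Yes. Falls are the one risk named in the Adverse Events section, they are in the risk assessment under Trial Management, and the stopping rules send a suspected fracture after a fall to emergency services.

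3. **Does another record close the gap?**
   - Self report logs (Usual care section): outside physical and occupational therapy only.
   - Adverse event form (Adverse Events): targeted treatment-related events and serious events, completed by the relevant therapist. It would show that some injurious falls occurred. No text sends it to the costing.
   - Serious adverse events (Assessment of safety): reported to the coordinating centre and then to the oversight committee. Again there is no link to costs, and the section on analysis populations plans no safety summaries.
   - Timing (Table 1): treatment ends at 8 weeks and follow-up is at 3 months, about 13 weeks. For roughly 13 − 8 = 5 weeks there is no scheduled contact with the therapist who completes the form.

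4. **Scale.** The background section says as many as 50% of stroke patients discharged to the community fall. Applied to 60 participants that is at most 0.5 × 60 = 30 fallers, but no time window is given and neither is the share needing care, so no expected cost follows.

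5. **Illustration on assumed unit costs only.** An event costing C adds C/20 to the mean of an arm of 20. If C is £2,000 to £10,000, that is £100 to £500 per participant. At an assumed £30 to £60 per session, 16 sessions cost £480 to £960. The ratio runs from 100/960 = 10% to 500/480 = 104%; with the dearer sessions the upper value is 500/960 = 52%. Two of the inputs are themselves unsettled in the protocol: the Duration section and the flow diagram give three sessions a week (3 × 8 = 24) instead of 16 in total, and the sample size section gives 50 patients, not 60. These statements need reconciling. The illustration shows that one event can move an arm mean visibly; it is not an estimate of the omission.

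**The case against.** Several arguments weigh on the other side.

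- **No explicit exclusion.** The sentence says what will be collected; it does not say that nothing else will be, and it does not mention falls. The cost forms are not shown, and the Trial Management section schedules preparation of cost recording for months 3 to 5, so their content could be wider. This stands: the gap is an inference from the qualifier.
- **Some events are captured elsewhere.** Falls outside the house, targeted adverse events and serious adverse events are all to be recorded, and many could be costed afterwards. This stands in part: the capture is narrower than the need and has no stated route into the cost analysis.
- **A condition-specific scope is defensible.** A perspective says whose costs count, not for which conditions, and relevance is left open. A reader might infer a flat contradiction with the perspective, or that all-cause collection is required. The protocol supports neither; all-cause collection is a preference. What remains is a mismatch between the stated aim and the narrow scope, at the point where the protocol names its own harm.
- **Carry-over to the definitive trial.** A reader might infer that the restricted form will simply be reused. The protocol says only that piloting will help to determine the later system, so it makes no such commitment.
- **Noise.** With 20 per arm, a single admission could dominate a mean. This stands, and it limits how the added costs should be read.

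**Conclusion.** The point holds as a cheap improvement to the cost collection. Taken as written, the wider service use covers stroke rehabilitation only, which leaves out hospital, emergency and GP care for injurious falls and falls short of the section's own aim of presenting all relevant costs. Adverse event reporting mitigates this without closing the gap.

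The size of the effect cannot be derived. The protocol gives no unit costs, no rate of injurious falls over 3 months and no expected difference between arms, and it calls the added risk of falling very small. A reader might infer from the illustration that the omitted cost could exceed the whole cost of delivery; that result appears only when the dearest assumed admission is paired with the cheapest assumed sessions. Nor does the protocol show that falls would be the main downstream cost of visual cue training.

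The conclusion rests on reading the qualifier literally and on the cost forms following it. Costing is not among the listed objectives, and recruitment, retention and completeness of outcome data are not affected.

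**What to change.** Amend the Health economic analysis section so that the resource-use form being piloted also asks about fall- and injury-related primary, secondary (including emergency) and social care contacts, in all three arms, at the 8-week and 3-month assessments. Report rehabilitation-specific cost as a separate subset, so that the narrower comparison stays visible. Present the fall- and injury-related costs descriptively, given arms of 20.

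The cost is a few more questions on a form that is still being piloted, and more variable cost data.
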